#### Metacognitions Questionnaire-30 *(MCQ-30)*

The MCQ-30 [37] is a 30-item self-report questionnaire used to measure metacognitive beliefs. It consists of five subscales; negative beliefs about uncontrollability of thoughts and danger; positive beliefs about worry; beliefs about need to control thoughts; cognitive confidence and cognitive self-consciousness. Higher scores indicate higher levels of maladaptive metacognition. The validity and reliability of MCQ-30 is well-established in adults [37].

#### Inventory of Interpersonal Problems *(IIP-64-C)*

This self-report measure [38] consists of 64 items: 39 items begin with: “It is hard for me to …” and 25 items introduce “Things that you do too much”. Each item is rated on a 5-point Likert scale, ranging from 0 (not at all) to 4 (extremely). The inventory is tapping eight specific interpersonal problem areas. Many studies have estimated Cronbach’s alpha for the IIP-64 scales in the range 0.72–0.85 [38–40], and test-retest correlation in the range of 0.56–0.83 [41].

#### Session Rating Scale *(SRS)*

The SRS [42] is a four-item visual analogue instrument designed to measure the quality of the working alliance on a session-to-session basis. Item analysis of the SRS provided a Cronbach’s alpha reliability coefficient of 0.88, and a test-retest reliability of 0.64.

#### The Posttraumatic Cognitions Inventory *(PTCI)*

The PTCI [43] is a widely used instrument to assess cognitions deemed to be important in the development and maintenance of posttraumatic symptoms. It consists of 36 items scored on a 7-point Likert scale. The instrument has excellent psychometric properties [43].

#### The WHO-5 Well-Being Index *(WHO-5)*

As a measure of overall psychological well-being we use the WHO-5 [44]. The instrument consists of five items measured on a 6-point Likert scale. The WHO-5 scale is considered a generic scale for the measurement of general well-being [45] and is deemed to have acceptable psychometric qualities [44] with a Cronbach coefficient alpha of 0.84 [46].

#### Sample size estimation

We assume similar post-treatment scores on the PDS as reported by Wells and colleagues [26] in their comparison of MCT with prolonged exposure, where M = 10.4 for MCT and M = 18.3 for the PE condition, with a pooled standard deviation of 10.6. It is estimated that for a two-tailed superiority trial, 58 patients are required in total (29 per arm) to have an 80% chance of detecting a significant difference in the primary outcome measure at the 5% level. We will aim to recruit more patients than this in order to compensate for dropouts.

### Procedure

The trial will be conducted at the specialist clinic for PTSD and traumatic stress at Nidaros DPS, St. Olavs hospital. Patients referred to the clinic will be screened and assessed for eligibility. Patients meeting the inclusion criteria will be invited to participate in the trial, and consent will be obtained by signing the form. Patients referred to the clinic who either (a) decline to participate in the trial or (b) do not meet the inclusion criteria but suffer from trauma-related symptomatology, will be given appropriate treatment as usual (TAU) at the clinic. Patients referred to the clinic who are not in the clinic target group, i.e. patients not suffering from trauma-related mental health problems, will be referred to other appropriate services.

The initial assessment will take approximately 90 minutes and will consist of carrying out a number of measures. Initially the Mini International Neuropsychiatric Interview (MINI) [47] will screen patients for PTSD symptoms and co-morbid Axis I disorders. If the inclusion criteria are met, then the above-described instruments will be administered, including those to assess primary PTSD symptoms, anxiety symptoms and comorbid mood disorders. Patients meeting the inclusion criteria and consenting to participate in the trial will be randomly allocated to the MCT condition or EMDR condition.

### Randomization

Participants meeting the inclusion criteria are randomized to either EMDR or MCT. Randomization is stratified on gender and borderline personality disorder characteristics, as both gender and BPD characteristics have been found/are assumed to impact treatment outcome. Before initiating the trial the principal investigator ([name]) generated a random-number table using SPSS. Due to the use of a printed random-number table the allocation is not absolutely/perfectly concealed. Authors [name] and [name] assign allegeable participants to the conditions based on the pre-defined random-number table.

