### Trial status

Recruitment is ongoing and the treatment phase is expected to be completed by the end of 2017.

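### Patients are assigned by trial authors from a printed table that the protocol admits is not fully concealed, and no safeguard is described for the remaining allocations

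*Protocol article*

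**What the plan says.** The Randomization section of the protocol article says that, before the trial started, the principal investigator "generated a random-number table using SPSS". Two authors then "assign allegeable participants to the conditions based on the pre-defined random-number table". The section states the consequence itself: "Due to the use of a printed random-number table the allocation is not absolutely/perfectly concealed". It also says: "Randomization is stratified on gender and borderline personality disorder characteristics".

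The Procedure section gives the order of events: "Patients meeting the inclusion criteria and consenting to participate in the trial will be randomly allocated to the MCT condition or EMDR condition". Eligibility and consent thus come before allocation. The trial runs at one specialist clinic. Trauma patients who decline or do not qualify "will be given appropriate treatment as usual (TAU) at the clinic".

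The Trial status section reads: "Recruitment is ongoing and the treatment phase is expected to be completed by the end of 2017".

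**The concern.** Concealment protects the step before randomisation. Whoever decides that a patient is eligible, or when to enrol that patient, should not be able to know the next assignment. Here the article describes its method and names the defect, so this is a flaw in a stated procedure and not a detail left to a fuller document. Admitting the defect does not remove it.

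There is some room for selection. Several exclusions in the Participants section involve clinical judgement, such as severe depression, acute suicidality and borderline personality disorder. Borderline characteristics are also a stratification factor because the authors regard them as related to outcome. A patient left out of the trial is still treated at the same clinic, so little stands in the way of exclusion or deferral.

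The later safeguards act too late or only in part. Intention-to-treat analysis protects the comparison only from randomisation onwards. The primary outcome is self-reported, and the Blinding section says that the blinding of assessors is uncertain. If prognosis differed between the arms because of who was enrolled, the superiority comparison would be biased, and analysis could not fully correct it.

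**Working it through.** **The plan's own figure.** The Sample size estimation section gives PDS means of 10.4 and 18.3 (difference 7.9), SD 10.6, two-sided 5% and 80% power. By the normal approximation, n per arm = 2 × (1.96 + 0.84)² × 10.6² / 7.9² ≈ 28.3, rounded up to 29, or 58 in total. This reproduces the stated figure. The method of allocation does not affect it.

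**Check of the text.** The concealment claim contains no number, so the sections were set side by side.
- Randomization: the table is printed and made in advance, authors assign from it, and concealment is admitted to be incomplete.
- Procedure: consent precedes allocation, but nothing is described that locks a patient's entry before the table is consulted.
- Blinding, Treatment adherence and fidelity, and Data analysis plan: none adds a safeguard on allocation or a sensitivity analysis for it.
- Trial status: recruitment continues.

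**Illustration of size.** The documents give neither a share of patients steered nor a difference in prognosis, so both are assumptions. Inputs: SD 10.6 and planned difference 7.9 (Sample size estimation); 100 patients (Abstract), taken as 50 per arm; true effect zero; unadjusted two-sample normal test.

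Standard error = 10.6 × √(2/50) = 2.12 points. Bias = (number of arms steered) × (share of the arm steered) × (shift in SD) × 10.6. The type I error is that of a two-sided 5% test whose statistic is shifted by bias / 2.12.

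| Assumed steering | Shift | Bias (points) | Share of 7.9 | Bias / SE | Type I error |
|---|---|---|---|---|---|
| 10% of one arm | 0.5 SD | 0.53 | 7% | 0.25 | 5.7% |
| 10% of one arm | 1 SD | 1.06 | 13% | 0.50 | 7.9% |
| 10% of both arms, opposite directions | 0.5 SD | 1.06 | 13% | 0.50 | 7.9% |
| 10% of both arms, opposite directions | 1 SD | 2.12 | 27% | 1.00 | 17.0% |

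**If only late patients are affected.** The number still to be allocated is not given. Assume 20, with 10% of them steered in opposite directions in both arms. The steered share of each arm is then 1/50 = 2%, and the bias is 2 × 0.02 × (0.5 to 1) × 10.6 = 0.21 to 0.42 points. The type I error is about 5.1 to 5.5%.

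**Sample size gives no protection.** For a fixed bias of 2 points, a t-test gives a type I error of 10.9% at 29 per arm and 15.4% at 50 per arm. Recruiting beyond 58 makes the false-positive rate from such a bias worse.

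**The case against.** The strongest reply is that much of the route to bias is inferred. The article does not say who can see the table, or when it is consulted. It puts eligibility and consent before allocation. It does not say that the assigning authors also screen, obtain consent, treat or assess. Screening and diagnosis use structured interviews, and borderline traits are counted by criteria. All of this stands, and it limits the point to a possibility.

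A reader might infer that remaining patients are being steered, or that staff know the next assignment before eligibility is settled. The documents support neither. They support only that nothing described would prevent it.

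The planned analysis also offers partial cover. The Data analysis plan tests group × time on the PDS and adds covariates where the arms are imbalanced. That can absorb some of a difference in measured baseline severity, but not a difference in unmeasured prognosis. The unadjusted figures above may therefore overstate the bias. The upper range also needs opposite steering in both arms across all 100 patients, which is a demanding assumption.

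Finally, little may be left to protect. Treatment is 12 weekly sessions and was expected to finish by the end of 2017, which puts the last allocation at about early October 2017. The article was published on 8 January 2018. It nevertheless says that recruitment is ongoing, so prospective concealment is worth having even if it reaches few patients.

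**Conclusion.** The point holds in limited form. The protocol states an allocation procedure with an admitted weakness in concealment, run by trial authors, and describes nothing that contains it. Selection by arm is possible but not shown.

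No size can be derived from the documents. Under the stated assumptions the bias runs from about 0.5 to 2.1 PDS points, or 7 to 27% of the planned difference, with a type I error of about 6 to 17% in an unadjusted comparison. It would be smaller if only remaining patients were affected or if the model absorbed part of the difference. These figures show what modest steering could do and do not estimate what happened.

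A reader might also conclude that a positive result would be worthless on this ground alone. That goes too far: for patients already allocated the weakness cannot be repaired, but it can be examined and reported openly.

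**What to change.** **Remaining patients.** Release each allocation only after eligibility, consent and baseline data have been logged irrevocably. Use sequentially numbered, opaque, sealed envelopes for each stratum, or an existing web randomisation service. The list should be held by an existing staff member with no role in eligibility, assessment or treatment.

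**Patients already randomised.**
- Check the assignments made against the table, within strata and in order of consent. The Study design section adds chronicity of PTSD to the two factors in the Randomization section, so first establish which strata the table used.
- Review the log of screened, excluded, declined and deferred patients against the allocation that was next at the time. Checking the sequence alone is not enough, because selective enrolment or deferral can leave the sequence intact.
- Analyse each patient in the arm that the table assigned.
- State in the report who had access to the table and when, and compare the arms at baseline.

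**Cost.** A short amendment, envelopes or access to an existing service, minor administration at each enrolment, and one review of at most 100 allocations together with the screening log. Sample size and treatments do not change.

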### Blinding

We aimed to make the assessors blind to the treatment the participants had received by assembling a team of assessors not involved in the treatment of the participants. However, since both therapists and assessors worked at the same outpatient clinic it is difficult to ascertain whether the assessors are indeed blind to the treatment the participants have received. However, due to logistical issues, two psychologists assigned to the assessor-team treated a couple of the participants in the trial. In these cases the assessors and the therapists were independent of each other, such as that a psychologist could not be the assessor and the therapist for the same patients.

### Plans to promote participant retention and complete follow-up

We will strive to collect data on all participants irrespective of whether they complete treatment or not. Data will primarily be collected through an electronic system/platform delivered by CheckWare (http://checkware.com/en). CheckWare is an internet-based system/platform for collecting, processing and saving sensitive information such as patient self-reports in a secure way. We believe this solution will ease the burden of self-report for the participants and facilitate the data collection. For participants who are unwilling or unable to make use of CheckWare we will provide the usual pen and pencil self-report forms. Participants will receive a notification delivered by SMS when it is time to complete 6-month and 12-month follow-up self-report assessments. Participants who do not complete these assessments will be contacted by telephone to assist them with any obstacles with completing the assessments. We will send an abbreviated pen and pencil version of the self-report package by ordinary mail to participants that do not respond to either the SMS notification or to the telephone call. Participants who are still unresponsive will be offered the possibility to come to the clinic to meet their clinician for more personalized follow-up, which includes completing an abbreviated pen and pencil version of the self-report package.

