#### Posttraumatic Diagnostic Scale *(PDS)*

The PDS [28] is a self-report diagnostic and symptom severity measure of PTSD based on the DSM-IV criteria. It consists of a total of 49 items. Of these, 17 items are related to diagnostic criteria as defined by the DSM-IV and these are rated on a 4-point Likert scale. The symptom severity score (PDS-SSS) was used to indicate severity of symptoms. Test-retest reliability over 3 weeks for the diagnosis of PTSD was acceptable (k = 0.74) and the validity is confirmed by high overlap between PDS and the structured clinical interview for PTSD (82%) [28].

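### The last-resort clinic visit ties the follow-up self-report to a meeting with the participant's clinician, which may expose a few 6- and 12-month PDS scores to therapist influence

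*Protocol article*

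**What the plan says.** The retention section of the protocol article describes a four-step ladder for the follow-up questionnaires.

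1. An SMS is sent "when it is time to complete 6-month and 12-month follow-up self-report assessments".
2. Non-completers are telephoned and helped with whatever stands in the way.
3. Those who respond to neither are sent a shortened paper package by post.
4. Anyone not reached by then "will be offered the possibility to come to the clinic to meet their clinician for more personalized follow-up". The questionnaire is tied to this visit, "which includes completing an abbreviated pen and pencil version of the self-report package".

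The routine route is the electronic platform, with paper forms for those who cannot or will not use it.

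The Blinding section states the aim of "assembling a team of assessors not involved in the treatment of the participants". For the few cases in which assessor-team psychologists also treated participants, it adds that nobody acted as both assessor and therapist for the same patient. The PDS, according to its own section, "is a self-report diagnostic and symptom severity measure of PTSD based on the DSM-IV criteria". The primary outcome is the PDS after treatment (3 months). That MCT remains superior at 12 months is the secondary hypothesis (Study design).

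**The concern.** The fourth step makes the self-report form part of a meeting with someone who knows the treatment arm and, most likely, delivered the treatment. Patients may report fewer symptoms to, or near, the person who treated them. The meeting is also further contact with that person around the time of measurement.

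Assessor blinding does not protect a self-reported scale. Its protection is that the patient answers away from the therapist, and this step weakens that. The patients concerned are not a random subset, since they reach the step by not responding.

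At stake is the 12-month PDS comparison, and with it the aim of comparing relapse between arms. The Discussion already names open follow-up and attrition as threats to the follow-up results. This step would add a third, avoidable one.

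**Working it through.** **Who is the clinician?** The text does not say outright. The independent staff are called assessors in the Blinding section, not clinicians. The Concomitant care section allows no other care during the trial apart from stable medication. So the clinician a participant has at this clinic is normally the trial therapist. The Discussion does allow further treatment afterwards, so a different clinician is possible. Nothing in the wording excludes the therapist.

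**Is the Blinding safeguard extended to this step?** No. The same-patient rule there concerns the assessor team, and the retention section neither repeats it nor refers to it.

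**Size.** The documents give neither the share of participants who reach the visit nor any reporting shift, so both are assumed. The reference figures come from the sample size section: means 10.4 and 18.3 (difference 18.3 − 10.4 = 7.9), SD 10.6, 29 per arm.

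*Plan's own figure.* n per arm = 2 × (1.960 + 0.842)² × 10.6² / 7.9² = 2 × 7.849 × 112.36 / 62.41 = 28.3, rounded up to 29, so 58 in total. This agrees with the protocol and is not in dispute.

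*Shift in one arm's mean* = share × shift in score. With a share of 5–15% and a shift of 3–6 points:
- smallest: 0.05 × 3 = 0.15
- largest: 0.15 × 6 = 0.90

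*Net bias in the contrast:*

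| Scenario | Calculation | Net bias (points) |
|---|---|---|
| Same uptake, same shift | cancels | 0 |
| Uptake 15% vs 5%, same shift | 0.10 × 3 to 0.10 × 6 | 0.3 to 0.6 |
| Same uptake (5–15%), shift 6 vs 3 | 0.05 × 3 to 0.15 × 3 | 0.15 to 0.45 |
| One arm only, share 5–20%, shift 2–4 | 0.05 × 2 to 0.20 × 4 | 0.1 to 0.8 |

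*Relative to the planned difference.* 0.3/7.9 = 3.8% and 0.6/7.9 = 7.6%. For the one-arm row, 0.1/7.9 = 1.3% and 0.8/7.9 = 10.1%.

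*Relative to sampling error.* The standard error of the difference at 29 per arm is 10.6 × √(2/29) = 2.78, taking the same SD at 12 months. Then 0.3/2.78 = 0.11 and 0.6/2.78 = 0.22 standard errors.

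**The case against.** The case for leaving the step alone is substantial. It is an offer, made only after three other attempts have failed, so few participants should reach it. The article does not say that the clinician is present while the form is filled in, helps with it or sees the answers. The procedure is the same in both arms, and equal use with equal effect drops out of the contrast. The Discussion cites attrition of 20 to 25% in PTSD trials as a source of bias, and a familiar face may bring back patients who would otherwise be lost. Losing them could bias the result as well. Even the assumed bias is a small fraction of a standard error.

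Most of this stands, and it limits the size of the point. It does not remove it. Completing the form within a meeting with the clinician is a stated procedure, and equal uptake cannot be taken for granted: the trial's own rationale is that exposure-based therapy may be harder for patients to tolerate, so non-response could differ by arm. The retention argument supports holding the meeting. It does not require the form to be completed during it.

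A reader might also infer from the shortened package that some of the 17 PDS symptom items are missing, so that no severity score could be computed. The documents do not support that. What is shortened is the package, which contains many instruments, and dropping secondary scales while keeping the PDS is at least as natural a reading. A journal article may leave the package contents to the full protocol.

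**Conclusion.** The concern holds in a limited form. The protocol places last-resort completion of the 6- or 12-month self-report within a visit to the participant's clinician, most naturally the unblinded therapist, and does not apply its own separation of assessors and therapists there. This may influence follow-up PDS scores in a small subgroup selected by non-response.

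The net bias at 12 months is 0.3 to 0.6 PDS points if uptake is 5% in one arm and 15% in the other and scores fall by 3 to 6 points. It is zero if uptake and influence are equal. The documents give none of these inputs, and the direction of any bias between arms is unknown.

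Stronger readings go too far. A reader might infer that hard-to-reach participants in general fill in the form in front of their therapist, but many may be recovered by telephone or post, and the therapist's presence during completion is not stated. A reader might infer that the trial's main result is compromised, but the ladder covers only the 6- and 12-month self-reports. The primary post-treatment PDS and the sample size are unaffected. The change is worth making because it is cheap, not because the likely bias is large.

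**What to change.** Amend the last step of the retention section along these lines: at a follow-up clinic visit the participant completes the self-report form, including the PDS, privately and seals it before any contact with the treating clinician. Where the participant accepts this, the form is handed out and collected by a member of the assessment team who did not treat them. Forms obtained at such visits are flagged, and the 12-month analysis is repeated without them as a sensitivity analysis.

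That repeat analysis turns flagged scores into missing values in a group selected by non-response. It should therefore be read alongside the main 12-month analysis, not in place of it.

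The cost is slight extra logistics with existing staff. A few patients might attend only to see their own therapist. They need not be lost, because that meeting can still take place once the form is sealed. The treatment phase was expected to end by the end of 2017, so 12-month assessments were still to come when the article appeared in January 2018, and the change could apply to them.
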